**Figure 2: fig2:**
[figure not shown]
Contact frequency and type throughout the 36-month lifestyle intervention. T: timepoints (months).

### Standard of care

Participants in the control group will receive general advice on physical activity and healthy eating, without individualized prescriptions from the transplant centre, reinforced during routine follow-up visits.

### Adherence and efficacy

Adherence to physical activity counselling will be assessed with IPAQ [13, 28], and adherence to dietary counselling with FFQ [29, 30]. Efficacy will be evaluated through routine clinical assessments, including blood chemistry parameters related to immunosuppressive therapy and cardiovascular risk, as well as nutritional status and dietary habits evaluation.

### Study outcomes

Outcome parameters will be assessed at predefined timepoints, as shown in Fig. 1. Study procedures will be performed in the specialized laboratories of IRCCS AOU Bologna and AUSL Romagna Hospitals according to standardized operating procedures. The sequence of assessments will be consistent across centres and timepoints.

### Primary outcome

The primary outcome is the change in estimated 10-year cardiovascular risk over 36 months, measured by the Framingham cardiovascular risk score. The primary analysis will compare the change in Framingham score between the lifestyle intervention and standard-of-care groups. The study is powered to detect a clinically meaningful between-group difference of 1 percentage point in the Framingham score.

### Secondary outcomes

#### Renal function

Renal function will be assessed by comparing eGFR, 24-h proteinuria, and urine albumin-to-creatinine ratio between the two groups. These measurements are collected according to clinical practice at each outpatient visit.

#### Gut microbiota

Gut microbiota composition will be analysed in faecal samples by 16S ribosomal RNA (rRNA) gene amplicon sequencing. After standardized collection, samples will be stored at low temperature, DNA will be extracted using validated kits, and the bacterial 16S rRNA gene will be amplified and sequenced on a high-throughput platform. Bioinformatic processing will provide relative abundances of the main bacterial taxa, which will be compared between groups.

#### Inflammatory profile

The inflammatory profile will be evaluated on fasting venous blood samples collected under standardized conditions. CRP and ferritin will be measured by high-sensitivity immunoassays, and IL-6 by multiplex immunoassay platforms. Samples will be processed promptly and stored at approximately −80°C until batch analysis.

#### IRCCS AOUBO research biobank

Additional blood, urine, and faecal samples will be collected and processed according to standardized biobanking procedures to ensure long-term sample integrity. Blood will be collected in appropriate tubes, and serum and plasma will be aliquoted and stored at −80°C. Urine will be collected as spot samples, aliquoted after laboratory processing, and stored at −80°C. Faecal samples will be self-collected, aliquoted, and rapidly frozen at −80°C to preserve microbial DNA and metabolites. All samples and clinical data will be pseudonymized and managed within the IRCCS biobank infrastructure in compliance with national and European standards.

#### IPAQ—International Physical Activity Questionnaire

The IPAQ is a self-report questionnaire used to assess physical activity in adults. The short form measures walking, moderate- and vigorous-intensity activity, and sitting time over the previous 7 days; responses are converted into metabolic equivalents of task (MET) -minutes per week and classified as low, moderate, or high physical activity levels using standardized scoring protocols [13].

#### Dietary adherence

Dietary intake will be assessed using a validated semiquantitative FFQ previously developed for Italian adults [14]. It captures habitual intake over the preceding 12 months by recording the frequency and portion size of foods and beverages, and nutrient intake will be estimated using standardized food composition databases.

#### Body composition

Body composition including fat-free mass, fat mass, and derived indices such as the fat-free mass index (FFMI) will be assessed by standardized multifrequency BIA according to European Society for Clinical Nutrition and Metabolism (ESPEN) recommendations [31].

### Intervention group procedures

In the intervention group, sports medicine centres will perform validated functional assessments, including the following tests.

#### 1-km walk test

The 1-km walk test is a submaximal test performed on a level treadmill at a constant, moderate intensity, monitored with the Borg 6–20 scale. When perceived exertion reaches 11–13, the test begins, and heart rate, walking speed, completion time, and perceived exertion are recorded to estimate aerobic capacity (VO₂peak/VO₂max) using validated equations [20].

#### Handgrip strength test

Handgrip strength is measured with a handheld dynamometer. Participants are usually seated with the shoulder adducted, elbow at about 90 degrees, and forearm in neutral position. They perform three maximal trials per hand, and the highest value is used for analysis [32].

#### 30-s sit-to-stand test

The 30-s sit-to-stand test is performed on a standard chair without armrests. Participants sit with feet flat on the floor and arms crossed over the chest, then stand and sit as many times as possible in 30 s. The score is the number of correctly completed stands [22].

#### Submaximal upper-limb strength test with free weights

Submaximal testing with free weights involves selecting an exercise for a specific upper-limb muscle group, such as biceps curl, triceps extension, or shoulder abduction, and choosing a load that can be lifted for 8–12 repetitions without volitional fatigue. After a standardized warm-up, repetitions are performed until full movement can no longer be completed, and the result is used to estimate maximal strength through prediction equations [24].

The nutritional intervention will be performed according to individual needs. BMI, eGFR, body composition, total estimated energy expenditure, caloric intake, personal food choices, and palatability will be taken into consideration to promote adherence to Italian nutritional guidelines to reduce cardiovascular risk considering simple sugars, lipid, and fibres intake. Protein intake will be tailored to each individual needs based on eGFR, age, body composition, BMI, and physical activity levels.

In those with a BMI >30, a personalized diet will be redacted aimed to also to obtain significant weight loss while simultaneously reducing cardiovascular risk.

### Statistical considerations

#### Sample size calculation

The sample size was estimated a priori based on the primary endpoint, the Framingham score. The study was powered to detect a between-group difference of 1 point, using parameters from a previous study with similar characteristics [33], including a standard of deviation (SD) of 8.1 and a correlation between repeated measurements of 0.95. With α = 0.05 and power of 80%, 198 participants completing follow-up (99 per group) were required. Assuming a 10% dropout rate, 220 participants will be enrolled; considering an expected 80% participation rate among eligible patients, ∼275 patients will be screened.

#### Statistical analysis plan

All analyses will follow the intention-to-treat principle. Baseline characteristics will be summarized using mean ± SD or median (interquartile range) for continuous variables and counts and percentages for categorical variables. The distribution of variables will be examined before inferential analyses. The primary endpoint will be analysed using repeated-measures analysis of covariance (ANCOVA) , with group, time, and group-by-time interaction as fixed effects and age, time from transplantation, and dialysis duration as covariates. The same framework will be applied to secondary continuous outcomes, including eGFR, gut microbiota composition, BMI, inflammatory markers, and quality of life. Potential effect modifiers will include sex, pretransplant and current physical activity, and dietary characteristics. Mean between-group differences in change in Framingham score will be reported with 95% confidence intervals, and subgroup analyses will be performed by sex and age group. If model assumptions are not met, nonparametric analyses will be used. Discrete outcomes, including hospital admissions, cardiovascular events, and death, will be analysed using binomial or multinomial logistic regression. Safety will be summarized by the frequency and type of adverse events in each group. Data from all centres will be pooled for analysis.

**Table 1: tbl1:** Inclusion and exclusion criteria.

Male and female patients who are KTRs stabilized from a clinical standpoint (judgment by the reference transplant centre) Minimum age: 30 years completed Maximum age: 69 years completed Time from transplant: from 6 months (after achieving clinical stability) to 10 years Organ function: eGFR (CKD-EPI 2021 formula) ≥30 ml/min/1.73 m² Obtaining informed consent
Patients unable to follow the prescription Recent acute cardiovascular event (<2 months) Unstable angina Hyperkinetic/hypokinetic arrhythmias not controlled with therapy, and with signs of haemodynamic compromise Severe aortic stenosis Heart failure class NYHA III and IV, ejection fraction (EF) <40% Acute diseases limiting physical activity practice Severe hypertension (baseline blood pressure (BP) ≥200/110 mmHg) Neuro-musculoskeletal pathologies that may be aggravated by exercise Patients unwilling to change lifestyle Any form of substance abuse, psychiatric disorder, or condition that, according to the investigator, may complicate physician–patient communication Pregnant women

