
## MATERIALS AND METHODS

### Study design and population

The KT-LIFESTYLE study is a pragmatic, multicentre, prospective, open-label, nonpharmacological randomized controlled trial. The primary endpoint is the between-group difference in change in the Framingham score over 36 months in KTRs receiving the lifestyle intervention versus standard of care. The Framingham score estimates the 10-year probability of a cardiovascular event using routinely collected clinical variables including sex, age, systolic blood pressure, smoking status, diabetes, high-density lipoprotein (HDL) cholesterol, and total cholesterol [11]. Secondary endpoints include renal function progression, assessed by eGFR calculated with the Chronic Kidney Disease Epidemiology Collaboration (CKD-EPI) 2021 formula [12], gut microbiota composition, body mass index (BMI), inflammatory markers [serum C-reactive protein (CRP), interleukin-6 (IL-6), and ferritin], metabolic assessment variation (including glucose and lipid profile) and adherence to physical activity counselling assessed by the International Physical Activity Questionnaire (IPAQ) [13], adherence to dietary counselling assessed by the Food Frequency Questionnaire (FFQ) [14], quality of life assessed by the Short Form-12 Health Survey (SF-12) [15], hospital admissions for significant clinical events, fatal and nonfatal cardiovascular events (major adverse cardiovascular events), and all-cause mortality. A maximal cardiopulmonary exercise test will be performed in a subgroup of 25 participants per group. No comparisons with the general population or other patient groups are planned. Annual interim analyses will assess data completeness, quality, and study conduct. Participants will be recruited from IRCCS AOU Bologna and AUSL Romagna Hospitals. The study population will include clinically, surgically, and functionally stable adult KTRs of both sexes followed in the outpatient setting. Participant enrolment will be based on the inclusion and exclusion criteria presented in Table 1. Written informed consent will be obtained from all participants, who will also complete baseline questionnaires on smoking status, alcohol consumption, pretransplant dialysis vintage, time since transplantation, cause of kidney failure, and comorbidities. Ethical approval (EM221-2025_138/2023/Sper/AOUBo) was obtained from the ethics committee. The study complies with the International Conference on Harmonization Good Clinical Practice guidelines and the Declaration of Helsinki.

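### The primary ANCOVA should adjust for the baseline Framingham score and name the month-36 group difference as its single test; the sample size can stay as it is

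*Protocol article*

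**What the plan says.** All places are in the protocol article.

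- **Study design and population:** "The primary endpoint is the between-group difference in change in the Framingham score over 36 months", intervention versus standard of care.
- **Primary outcome:** "The primary outcome is the change in estimated 10-year cardiovascular risk over 36 months", and "The primary analysis will compare the change in Framingham score between the lifestyle intervention and standard-of-care groups". The trial is "powered to detect a clinically meaningful between-group difference of 1 percentage point in the Framingham score".
- **Sample size calculation:** the inputs are "a standard of deviation (SD) of 8.1 and a correlation between repeated measurements of 0.95". The result is "With α = 0.05 and power of 80%, 198 participants completing follow-up (99 per group) were required".
- **Statistical analysis plan:** the primary model is a repeated-measures ANCOVA "with group, time, and group-by-time interaction as fixed effects and age, time from transplantation, and dialysis duration as covariates". The section also undertakes to give the group differences in change as means with 95% confidence intervals. It extends the same model to the secondary continuous outcomes, among them eGFR, BMI, inflammatory markers and quality of life.

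The analysis section does not list the baseline Framingham score as a covariate. It does not say whether baseline is one of the repeated time levels, and it does not name which group-by-time contrast is the primary test.

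**The concern.** The sample size and the model description do not quite meet. The calculation borrows nearly all its precision from "a correlation between repeated measurements of 0.95", so the primary test must use each patient's own baseline. The model has an explicit covariate list from which the strongest available predictor, the baseline score, is absent. It offers three fixed effects without saying which one carries the primary test.

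Two things are at stake. First, change over 36 months can be tested in more than one way: as the change at month 36, as the average change over follow-up, or as any difference between the two trajectories. These have different power and may give different p-values. In an open-label trial the choice should be fixed in advance. Second, a change score without baseline adjustment wastes some precision. The waste is small when the correlation is 0.95 and grows as it falls, which is relevant to the secondary outcomes that inherit the model.

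**Working it through.** **Inputs.** From the article: difference 1 point, SD 8.1, correlation ρ = 0.95, α = 0.05, power 80%, 99 completers per group. Sidedness is not stated and two-sided is assumed; one-sided testing would need only 80 to 82 per group and does not match the plan.

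**1. Reproducing the plan's figure.** Per group, n = 2 × SD² × (1.960 + 0.842)² / 1².

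- Month-36 score adjusted for baseline: SD = 8.1 × √(1 − 0.95²) = 2.529, giving n = 100.4, so 101.
- Change score: SD = 8.1 × √(2 × (1 − 0.95)) = 2.561, giving n = 103.0, so 103.
- SD 8.1 with no use of baseline: n = 1,030.

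The stated 99 is close to the first two and nowhere near the third, so the calculation presupposes that baseline is used. The later steps also reproduce: 198 / 0.90 = 220 and 220 / 0.80 = 275.

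**2. Power of a single month-36 contrast at 99 per group.** The noncentrality is 99 / (2 × SD²), and power is approximately Φ(√noncentrality − 1.960).

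- Change from baseline: 99 / (2 × 6.561) = 7.545, power 78.4%.
- Baseline as covariate: 99 / (2 × 6.397) = 7.738, power 79.4%.

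With the noncentral t distribution these become 78.0% and 79.0%.

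**3. Variance gained by adjustment.** Adjusted variance over change-score variance is (1 − ρ²) / (2(1 − ρ)) = (1 + ρ)/2.

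- ρ = 0.95: 0.975, a cut of 2.5%.
- ρ = 0.80 (assumed; the article gives no correlation for the secondary outcomes): 0.90, a cut of 10%.

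**4. Other tests of change that the wording leaves open.** These assume visits at 0, 12, 24 and 36 months (the schedule figure is not shown) and compound symmetry.

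For the overall group-by-time test on 3 degrees of freedom, the noncentrality is (99/2) / (8.1² × 0.05) × Σ(dᵢ − d̄)² = 15.09 × Σ(dᵢ − d̄)², where dᵢ is the group difference at visit i.

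- Effect growing linearly (0, 1/3, 2/3, 1): Σ = 0.556, noncentrality 8.38, power 67.7% by chi-square and 67.4% by F.
- Constant effect (0, 1, 1, 1): Σ = 0.75, noncentrality 11.32, power 81.6% by chi-square, about 81% by F.

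For the average of the three post-baseline changes, the variance is 8.1² × [(1 + 2 × 0.95)/3 + 1 − 2 × 0.95] = 4.374, so SD = 2.091.

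- Linear effect (mean 2/3): power 61.1%.
- Constant effect (mean 1): power 92.0%.

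**The case against.** The best defence is that the target is already fixed. Three sections of the article speak of a between-group difference in change. If baseline is a level of the repeated outcome, the baseline-to-month-36 group-by-time contrast is that difference, and leaving baseline off the covariate list is then normal practice. Power falls short of the adjusted analysis by only about one percentage point. This stands.

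Chance imbalance at baseline is also a weak argument for the primary outcome. At ρ = 0.95 with equal SDs, a change score passes on 5% of an imbalance. One standard error of imbalance is 8.1 × √(2/99) = 1.15 points, which moves the estimate by about 0.06. Randomisation is moreover stratified by sex and age, both of which enter the score. This stands too.

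A reader might infer from the covariate list that power collapses: to about 14% if follow-up scores were analysed with no baseline information and the listed covariates explained nothing, or to 7–10% if the group main effect were tested with baseline among the time levels. The article does not support that. Neither analysis estimates a difference in change, which is what it says it will compare and report.

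Finally, an article condenses a fuller plan, and an unseen SAP may settle the contrast. That is a fair reason not to fault missing detail such as the covariance structure. It does not remove the point, because the article does set out the primary model with an explicit covariate list, and that list can be improved as it stands.

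**Conclusion.** The point holds as a low-cost improvement to a stated model. It is not a fault that undermines the trial. The covariate list omits the baseline value of the outcome, and no contrast is named as primary, although the sample size depends on baseline being used.

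On the natural reading the cost of the omission is about one point of power (78% against 79%) and 2.5% of variance. The gain is larger for any secondary outcome with a weaker correlation. The open choice of test matters more: an overall interaction test would have about 67% power under a linearly growing effect, although about 81% under a constant one. Nothing in the article says that the overall test is intended.

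The single-contrast figures rest on the article's SD and correlation and on two-sided testing. The interaction and average-change figures also rest on the assumed yearly visits and compound symmetry. The 10% figure rests on an assumed correlation of 0.80. None of this calls for a different sample size.

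**What to change.** In the Statistical analysis plan section:

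- Model the post-baseline Framingham scores, with the baseline score added to the three listed covariates. Baseline should then not also be a level of the repeated outcome.
- Name the between-group difference at month 36, with its 95% confidence interval, as the single primary test. Other visits and the overall interaction are supportive.
- For the secondary continuous outcomes under the same framework, adjust each for its own baseline value.

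The covariance structure and any baseline-by-visit term can be left to the SAP. If a fuller plan already says this, bring the published wording into line with it.

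The cost is a few sentences and one model degree of freedom for the baseline term. The score's components are collected routinely, so there are no new data, no extra patients and no change to the 220 to be enrolled.

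### 16S relative abundances are assigned to the Framingham ANCOVA, which ignores that shares sum to one and can show apparent differences in taxa that did not change

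*Protocol article*

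**What the plan says.** Three places in the protocol article bear on this.

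- **Study design and population** lists "gut microbiota composition, body mass index (BMI), inflammatory markers" among the secondary endpoints.
- **Gut microbiota** (under Secondary outcomes) fixes the assay, "Gut microbiota composition will be analysed in faecal samples by 16S ribosomal RNA (rRNA) gene amplicon sequencing", and the variable: "Bioinformatic processing will provide relative abundances of the main bacterial taxa, which will be compared between groups".
- **Statistical analysis plan** gives the model, "The primary endpoint will be analysed using repeated-measures analysis of covariance (ANCOVA) , with group, time, and group-by-time interaction as fixed effects", and extends it: "The same framework will be applied to secondary continuous outcomes, including eGFR, gut microbiota composition, BMI, inflammatory markers, and quality of life". Age, time from transplantation and dialysis duration are the covariates. One general fallback follows: "If model assumptions are not met, nonparametric analyses will be used".

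The article does not say that taxa are tested one at a time. It gives no taxonomic rank, no number of taxa and no transformation of the shares.

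**The concern.** An ANCOVA needs a single number per participant and visit. A microbial composition is a set of shares that must add to one, and the only single numbers the article derives from it are the shares of individual taxa. The stated model therefore most naturally becomes one ANCOVA per taxon on its share.

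That model treats each share as if it could move independently of the others, which it cannot. If diet or exercise enlarges one abundant taxon, every other taxon's share falls even where the amount of that organism is the same. The test then picks up a between-arm difference in a taxon that did not respond.

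The mechanistic reading is at stake. The article's Conclusions and Potential impact paragraphs promise insight into how lifestyle acts on the microbiota and how individual taxa relate to cardiovascular risk. Because the intervention is partly dietary, a real shift in some taxon is plausible, and that is the condition under which the problem appears.

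**Working it through.** **1. The plan's own figures.** The article states no number of taxa, power or error rate for the microbiota, so there is no figure to reproduce for this outcome. Only the arm size is borrowed: "With α = 0.05 and power of 80%, 198 participants completing follow-up (99 per group) were required". That size follows closely from the stated SD of 8.1, correlation of 0.95 and difference of 1 point (two-sided test assumed):

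- residual variance = 8.1² × (1 − 0.95²) = 65.61 × 0.0975 = 6.397, so residual SD = 2.529
- n per arm = 2 × (1.960 + 0.842)² × 6.397 / 1² ≈ 100.4, rounded up to 101, against the stated 99 (power 79.4% at 99)

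This confirms the arm size used below and has no other bearing on the point.

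**2. Size of the closure effect.** Let one taxon have share p and multiply by f, with all others unchanged in amount. The total becomes 1 + p(f − 1), so at average abundances each unchanged taxon's share is multiplied by 1 / [1 + p(f − 1)].

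| Share p | Fold f | Multiplier for unchanged taxa | Apparent fall in share |
|---|---|---|---|
| 10% | 1.5 | 1/1.05 = 0.952 | 4.8% |
| 30% | 1.25 | 1/1.075 = 0.930 | 7.0% |
| 30% | 1.5 | 1/1.15 = 0.870 | 13.0% |
| 30% | 2 | 1/1.30 = 0.769 | 23.1% |

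**3. How often a test detects that fall.** Simulation inputs, all assumed except the arm size: 99 per arm, 20 taxa, log-normal amounts with log-SD 0.6, baseline to follow-up correlation 0.5, one taxon truly changed in the intervention arm, two-sided 0.05 per test, 600 replicates for the ANCOVA columns. The model is a simplified form of the plan's: one follow-up value, adjusted for baseline, without the clinical covariates. The log-ratio column uses each taxon's log share minus the participant's median log share. Entries are mean rejection rates over the 19 unchanged taxa.

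| Changed taxon | ANCOVA on shares | Rank test, change in share | Rank test, follow-up share | ANCOVA on log-ratios |
|---|---|---|---|---|
| None | 5.0% | – | – | 5.0% |
| 10% share, ×1.5 | 9% | 8% | 8% | 5.1% |
| 30% share, ×1.25 | 12% | 11% | 12% | 4.8% |
| 30% share, ×1.5 | 30% | 26% | 31% | 4.9% |
| 30% share, ×2 | 76% | 66% | 75% | 5.5% |

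Repeat runs of the design agree to within about a percentage point: about 8% to 9% in the mildest case and about 75% in the strongest. The rank columns come from one of these repeats.

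**4. Sensitivity to between-person spread.** Raising the log-SD from 0.6 to 1.0 lowers the last case (30% share doubling) from about 75% to about 23%. A separate design with 60 taxa and a 20% share doubling flags, out of 59 unchanged taxa, 27.8 at log-SD 0.6, 7.6 at 1.0 and 3.3 at 1.5, where chance alone gives 59 × 0.05 ≈ 3.0.

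**5. Would a multiplicity rule cure it?** No. With Bonferroni over 20 taxa, at least one unchanged taxon is still flagged in 12%, 18%, 64% and 99.7% of runs, in the order of the table. The shift in share is systematic, so a stricter threshold only delays its detection.

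**The case against.** **Per-taxon testing is inferred.** Neither section says it. This stands as a limit on the wording. It is still the natural reading, because the article defines no other scalar for the model to use.

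**The fallback covers skew and zeros.** In general terms it does, so non-normality should not carry the point. It does not cover closure: the rank columns above are nearly as affected as the ANCOVA.

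**The outcome is defined as relative abundance, so a difference in share is real.** This is the strongest objection, and it stands. A reader might infer that the plan creates false differences. It does not, in the sense that a fall in share is a true fall in share. The error arises when that fall is read as a change in the organism itself, and with no true shift anywhere the per-taxon error stays at 5%.

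**A reader might also infer that most reported taxa would be spurious.** The article supplies no shares, fold-changes or spread to support that. Results range from near chance to most unchanged taxa, depending on inputs it does not give.

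**No multiplicity rule across taxa is stated.** For a secondary sequencing outcome, this is commonly left to the statistical analysis plan, which is not shown. It is not part of this point.

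**Conclusion.** The point holds in a limited form. The article assigns 16S shares to a model built for one continuous score. This is a stated choice, not a gap left by condensing, and it suits compositional data badly. When an abundant taxon truly changes, unchanged taxa can show apparent between-arm differences at rates from about 8% to about 75% at log-SD 0.6, against a nominal 5%. The excess shrinks as between-person spread grows and disappears if nothing changes.

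These rates rest on assumed taxon numbers, shares, fold-changes and spread, on the per-taxon reading, and on a simplified model. The near-5% result for log-ratios also assumes that most taxa are unchanged, because sequencing alone does not give absolute amounts.

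The outcome is secondary. The Framingham analysis, the sample size and the conduct of the trial are not touched.

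**What to change.** In the Statistical analysis plan section, remove gut microbiota from the list of outcomes sharing the primary model and add a sentence along these lines: *Bacterial taxa will be analysed on a log-ratio scale, adjusted for the baseline value, with a stated rule for zero counts; one global test will compare the change in overall composition between arms.* Where raw shares are shown, word the conclusion as a change in relative share only.

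Name the reference for the log-ratio. The check above used the participant's median. Centring on the mean log share passes a small part of the shift on: with 20 taxa and one doubling, each unchanged taxon moves by −ln(2)/20 = −0.035 on the log scale, about 3.4%, against 23.1% on the raw share in the 30% case.

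The cost is analysis code, a decision on zeros and a less direct interpretation than a percentage share. No new samples or visits are needed. The change is best made before between-arm microbiota results are examined.

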
### Randomization

Participants will be randomized 1:1 to the lifestyle intervention group, receiving individualized exercise prescription plus dietary counselling, or to the control group, receiving standard lifestyle advice. Randomization will be stratified by sex and age in 5-year intervals and performed using a secure electronic randomization system [16].

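### Logistic regression suits recurrent hospital admissions poorly and, for cardiovascular events and death, cannot use partial follow-up

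*Protocol article*

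**What the plan says.** The section on study design and population lists among the secondary endpoints "hospital admissions for significant clinical events, fatal and nonfatal cardiovascular events (major adverse cardiovascular events), and all-cause mortality". The statistical analysis plan section then fixes one family of models for all three: "Discrete outcomes, including hospital admissions, cardiovascular events, and death, will be analysed using binomial or multinomial logistic regression". It also states: "All analyses will follow the intention-to-treat principle".

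The horizon is a common 36 months. The sample size section expects incomplete follow-up: "Assuming a 10% dropout rate, 220 participants will be enrolled". It gives no split of that dropout between the groups, and no event rates for admissions, cardiovascular events or death. The article does not say how a participant enters the logistic model after leaving before month 36 or after more than one admission. Safety is to be summarised by frequency and type of adverse event, which does not supply a time-based analysis of these endpoints.

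**The concern.** The three outcomes differ in kind. Admissions can recur, cardiovascular events have dates, and death ends follow-up. A binomial logistic model reduces each to whether at least one event occurred, and uses neither the number of events nor the time for which each participant was observed.

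Two things are at stake. For admissions, information is discarded and power falls. For all three, some participants will be observed for less than 36 months, and logistic regression has no natural place for partial follow-up. Contact is much more frequent in the intervention group (scheduled calls and dietitian visits) than in the control group (general advice at routine visits), and the trial is open-label. Retention could therefore differ between groups, in either direction.

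The model is stated outright, so this is not a detail that the article leaves to a fuller plan.

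**Working it through.** **The plan's own figure.** The only stated design figure is for the Framingham score (difference 1, SD 8.1, correlation 0.95, α 0.05, power 80%, 99 per group). With two-sided α and the ANCOVA residual SD, 8.1 × √(1 − 0.95²) = 2.529, and n = 2 × (1.960 + 0.842)² × 2.529² ≈ 100.4, so 101 per group or 202 in total. That is close to the stated 198. Then 198/0.90 = 220. These figures stand and do not depend on the event outcomes.

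**Inputs for the event outcomes.** From the article: 220 participants allocated 1:1 (110 per group), 36 months, 10% dropout. Assumed, because the article gives none: event rates, overdispersion, rate ratio and split of dropout by group.

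**A. Admissions: power with complete follow-up.** Counts are negative binomial with mean m over 3 years and dispersion 1; the rate ratio is 0.70.
- Probability of any admission: p = 1 − 1/(1 + m).
- Logistic: SE of the log odds ratio = √[1/(110·p₀(1−p₀)) + 1/(110·p₁(1−p₁))].
- Rate model: SE of the log rate ratio = √[(1/m₀ + 1)/110 + (1/m₁ + 1)/110].

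At 0.4 per year, m₀ = 1.2 and m₁ = 0.84, so p₀ = 0.545 and p₁ = 0.457. With dispersion 1 the odds of any admission equal m, so the odds ratio is also 0.70 and its log is −0.357. The logistic SE is 0.271 (z = 1.32, power 26.0%). The rate-model SE is 0.191 (z = 1.86, power 46.2%).

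| Control rate per year | Logistic power | Rate-model power | Information kept by logistic (ratio of z²) |
|---|---|---|---|
| 0.1 | 18% | 22% | 80% |
| 0.3 | 25.6% | 40.7% | 57% |
| 0.4 | 26.0% | 46.2% | 50% |
| 0.5 | 25.7% | 50.3% | 44% |

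A simulation with 10% dropout in both groups, control rates of 0.1 to 0.5 and dispersion 0.5 to 2 agrees. Power is 0.14 to 0.31 for logistic and 0.19 to 0.61 for a rate analysis, and 18% to 66% of control-group admissions are repeats. Type I error is near nominal for both (0.044 to 0.056 and 0.046 to 0.059).

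**B. Cardiovascular events and death: power with complete follow-up.** With a hazard ratio of 0.70, 110 per group and control rates of 0.01 to 0.05 per person-year, power is 6.1% to 14.5% for logistic regression and for a hazard-ratio analysis alike. The two agree to within 0.1 percentage point.

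**C. Bias from partial follow-up, no true effect.** Event times are exponential with rate r. A fraction d drops out uniformly over 3 years, and dropouts without an observed event are counted as event-free. The observed event probability is

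p = (1 − d)(1 − e^(−3r)) + d[1 − (1 − e^(−3r))/(3r)].

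At r = 0.4 the full-follow-up probability is 0.699 and the dropout probability 0.418. With 5% control and 15% intervention dropout, p = 0.685 and 0.657, which gives an odds ratio of 0.88.

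| Dropout, control v intervention | Null odds ratio, r = 0.02 | r = 0.05 | r = 0.2 | r = 0.4 |
|---|---|---|---|---|
| 10% v 10% | 1.00 | 1.00 | 1.00 | 1.00 |
| 5% v 15% | 0.95 | 0.94 | 0.92 | 0.88 |
| 0% v 20% | 0.90 | 0.89 | 0.85 | 0.77 |

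The group with more dropout looks protected. Reversing the imbalance reverses the direction.

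**The case against.** The case for leaving the sentence alone has force.

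- **Logistic regression can be valid here.** The horizon is common to all. If status at month 36 is known for everyone, it is a sound comparison of 36-month risk, and someone who dies without the event is correctly a non-event at that horizon. Visits follow routine transplant care, so people who leave the programme may still be traced. The 10% is sized on completing follow-up for the Framingham endpoint; the article does not say that these people are lost for admissions or death. This stands, and makes the bias conditional.
- **Intention-to-treat.** A reader might infer that the model contradicts the intention-to-treat commitment. It does not. That principle governs analysis by allocated group; partial follow-up is a missing-data matter.
- **General loss of power or of most information.** A reader might infer either. Part B shows no material power loss for cardiovascular events or death. For admissions, logistic keeps 44% to 57% of the information at 0.3 to 0.5 per year and 80% at 0.1 per year, so the loss is about half at most of the rates examined. The endpoint covers only significant clinical events in stable recipients, so a low rate is possible.
- **Competing risks.** Cardiovascular death is already part of the endpoint, so only non-cardiovascular death competes.
- **Multinomial models.** Categories such as 0, 1 and 2 or more admissions would recover some of the repeats. The article does not say this is intended, and time at risk would still go unused.
- **The alternative has assumptions too.** Censoring at last contact must be taken as non-informative.

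What survives is the mismatch for admissions and the lack of any means to use partial follow-up.

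**Conclusion.** The point holds in limited form and deserves correction, though not as a major flaw.

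For admissions, the stated model gives about 26% power where a rate model on the same data gives 41% to 50%, under assumed rates of 0.3 to 0.5 per patient-year, rate ratio 0.70, dispersion 1 and 110 per group. At 0.1 per year the gap is small (18% against 22%). Even the better model is underpowered, so estimates will be imprecise either way.

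For cardiovascular events and death, the issue is partial follow-up rather than power. The null odds ratio moves to between 0.95 and 0.77 only if dropout differs between groups, dropouts are not traced to month 36, and they are counted as event-free. The article establishes none of these conditions; it gives only an overall 10%. With equal dropout there is no bias under the null.

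These are secondary outcomes. The Framingham analysis and the sample size are untouched.

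**What to change.** Replace the sentence on discrete outcomes so that:
- hospital admissions are analysed by negative binomial regression with log follow-up time as offset, reporting a rate ratio with 95% CI;
- cardiovascular events and all-cause death are each analysed as time from randomisation to first event, censored at last contact, with a Cox hazard ratio and 95% CI;
- cumulative incidence is shown, with non-cardiovascular death as a competing event for cardiovascular events;
- sparse events are reported descriptively with exact intervals.

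The cost is a change of wording, with no change to sample size or visits. Event dates and last-contact dates must be recorded; the article does not say that they are, and it is assumed here that routine follow-up supplies them. Censoring must be assumed non-informative. Making the change before outcome data are compared by group avoids a post hoc choice of model.
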